### **9.2. Subject Exclusion Criteria**

Subjects must not have met any of the following exclusion criteria to be eligible for enrollment into the study:

#### **9.2.1. Prior Treatment**

1. Use of chemotherapy, hormonal therapy, immunotherapy, or any other anticancer or experimental therapy  $\leq 28$  days prior to Cycle 1 Day 1.
2. Radiotherapy to  $\geq 30\%$  of the bone marrow.
3. Surgery  $\leq 28$  days prior to Cycle 1 Day 1 (minimally invasive procedures for the purpose of diagnosis or staging of the disease are permitted).
4. Prior therapy with cetuximab.
5. Prior therapy with panitumumab.
6. Prior therapy with pomalidomide (CC-4047), lenalidomide, or thalidomide.

#### **9.2.2. Laboratory**

7. Absolute neutrophil count (ANC)  $< 1.5 \times 10^9/L$ .
8. Platelet count  $< 100 \times 10^9/L$ .
9. Creatinine Clearance  $< 50$  mL/min (by Cockcroft- Gault).
10. Bilirubin  $> 1.5 \times$  ULN ( $> 2.0 \times$  ULN in the presence of Gilbert's Syndrome).
11. Serum AST or ALT  $> 3.0 \times$  ULN ( $> 5 \times$  ULN in the presence of liver metastases).
12. Hemoglobin  $< 9$  g/dL.

#### **9.2.3. Other Disease State**

13. Untreated, symptomatic brain metastases (brain imaging not required).
14. Venous thromboembolism  $\leq 6$  months prior to Cycle 1 Day 1.
15. Current congestive heart failure (New York Heart Association class II-IV).
16. Myocardial Infarction (MI)  $\leq 12$  months prior to Cycle 1 Day 1.
17. Uncontrolled hypertension.
18. Prior malignancies within 5 years, with the exception of treated basal cell/squamous cell carcinoma of the skin or "in-situ" carcinoma of the cervix or breast.

**9.2.4. General**

19. Any condition (psychological, familial, sociological or geographical), including the presence of laboratory abnormalities, which would place the subject at unacceptable risk if he/she were to participate in the study, confound the ability to interpret data from the study, or not allow the subject to comply with the requirements of the study protocol.
20. Pregnant or lactating women.

## **10. DESCRIPTION OF TREATMENT**

### **10.1. Study Treatment**

#### **10.1.1. Lenalidomide**

Celgene Corporation will supply lenalidomide as 5, 10, 15, 20, and 25 mg capsules to be administered PO once daily for Days 1-28 of each 28-day treatment cycle. Study drug will be packaged in bottles containing enough capsules for 28 days of dosing. All subjects will be required to take a single capsule each day for Days 1-28 of each cycle. Lenalidomide should be taken at approximately the same time each day.

#### **10.1.2. Cetuximab**

Celgene Corporation will supply commercial cetuximab labeled as IMP for administration via IV infusion on Days 1, 8, 15, and 22 of each 28-day cycle. Cetuximab will be administered at 400 mg/m^2 initial dose, then 250 mg/m^2 weekly.

### **10.2. Treatment Assignments**

Subjects meeting all eligibility criteria will be enrolled into the study via IVRS. Dose levels will be determined according to Section 8. Treatment with investigational products will continue in 28-day cycles until disease progression, unacceptable toxicity or treatment discontinuation for any other reason.

### **10.3. Dose Modification or Interruption**

Dose modifications of lenalidomide and cetuximab are not permitted during Cycle 1 of the Phase 2a – Safety Lead-In part, unless a subject experiences a DLT, however permitted anytime after Cycle 1 during Phase 2a – Safety Lead-In, anytime during Phase 2b –POC and Phase 2b – Expansion.

For toxicities consistent with cetuximab administration, discontinuation, dose interruptions and/or reductions see Section 10.3.2 and the approved product labeling. If toxicities are believed to be attributed to lenalidomide administration, please see Table 6 for dose modification guidelines. Doses of any investigational product cannot be re-escalated once reduced. Any investigational product (lenalidomide and/or cetuximab) held > 14 days must be discontinued. If cetuximab is discontinued per protocol and for reasons other than disease progression, lenalidomide may be continued until documented tumor progression, unacceptable toxicity, death, or treatment discontinuation for any other reason.

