### **8.1.2. Safety Lead-In Definition of Dose Limiting Toxicity**

DLT is defined as one or more of the following:

- Total of  $\geq 7$  days of lenalidomide and/or  $\geq 1$  dose of cetuximab missed during the first cycle due to drug-related toxicity as outlined below:
  - Any Grade 3 or 4 non-hematological toxicity (excluding alopecia), even after optimally treated with supportive measures.
    - A rash with suspected relationship to cetuximab, treated and resolved in accordance with the guidelines will not be considered a DLT.
  - Grade 4 neutropenia or febrile neutropenia.
  - Grade 4 thrombocytopenia.

Should any subject discontinue the study prior to completing the entire first cycle for reasons other than a DLT or if  $\geq 7$  days of lenalidomide and/or  $\geq 1$  dose of cetuximab were missed during the first cycle for reasons other than a DLT, then a replacement subject will be added at that dose level.

The occurrence of one of the above drug-related toxicities will result in a clinical and/or laboratory assessment to be performed within 7 days following the initial finding to examine the subject for resolution of the toxicity. Lack of resolution of any of these toxicities according to the guidelines above or within 7 days of scheduled start of Cycle 2 Day 1 will be considered a DLT. Subjects who experience a DLT may continue on treatment at the Investigator's discretion at a lower dose of lenalidomide in accordance with [Table 6](#).

Adverse events will be graded using the CTCAE Version 4.0 ([http://ctep.cancer.gov/protocolDevelopment/electronic\\_applications/docs/ctcae4.pdf](http://ctep.cancer.gov/protocolDevelopment/electronic_applications/docs/ctcae4.pdf)).

If cetuximab is discontinued, lenalidomide may be continued until documented tumor progression, unacceptable toxicity, death, or treatment discontinuation for any other reason.

Following Cycle 1, all subjects will continue on assigned treatment until documented tumor progression, unacceptable toxicity, death, or treatment discontinuation for any other reason and be followed for toxicity and secondary endpoints.

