| Neutropenia                                                         | 3 / 4 | Hold lenalidomide, CBC weekly until resolution to $\leq$ Grade 2, resume lenalidomide at 5 mg reduction in dose. Additional dose reductions are permitted to a minimum of 5 mg.                                                                                                                      |
| Thrombocytopenia                                                    | 3 / 4 | Hold lenalidomide, CBC weekly until resolution to $\leq$ Grade 2, resume lenalidomide at 5 mg reduction in dose. Additional dose reductions are permitted to a minimum of 5 mg.                                                                                                                      |
| Venous thrombosis or embolism                                       | 3     | Continue lenalidomide and anticoagulate.                                                                                                                                                                                                                                                             |
|                                                                     | 4     | Discontinue lenalidomide and anticoagulate.                                                                                                                                                                                                                                                          |
| Allergic reaction or hypersensitivity                               | 2 / 3 | Hold lenalidomide until resolution to $\leq$ Grade 1; resume lenalidomide at 5 mg reduction in dose. Additional dose reductions are permitted to a minimum of 5 mg.                                                                                                                                  |
|                                                                     | 4     | Discontinue lenalidomide.                                                                                                                                                                                                                                                                            |

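### Section 10.3 does not say whether its Cycle 1 bar on dose modification in the lead-in covers holds, so it conflicts with Table 6 and leaves DLT or replacement status open to reading; the synopsis and Section 8.1.2 also define DLT differently

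*Protocol*

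**What the plan says.** Section 10.3 states that, for lenalidomide and cetuximab alike, dose modifications "are not permitted during Cycle 1 of the Phase 2a – Safety Lead-In part, unless a subject experiences a DLT". They are allowed at any later time and in both Phase 2b parts.

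Section 8.1.2 builds its DLT definition on missed treatment: at least 7 lenalidomide days and/or at least one "dose of cetuximab missed during the first cycle due to drug-related toxicity as outlined below". The toxicities nested beneath are any Grade 3 or 4 non-hematological toxicity (with exceptions for alopecia and for a cetuximab rash that is treated and resolves), "Grade 4 neutropenia or febrile neutropenia" and "Grade 4 thrombocytopenia". A later sentence in the same section adds a second route: "Lack of resolution of any of these toxicities according to the guidelines above or within 7 days of scheduled start of Cycle 2 Day 1" is also a DLT. A subject who misses the same amount of drug for reasons other than a DLT is replaced.

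Table 6, in Section 10.3.1, has a column headed as dose modification that contains holds, reductions and discontinuations. For Grade 3 or 4 neutropenia and thrombocytopenia it reads "Hold lenalidomide, CBC weekly until resolution to" Grade 2 or lower, then "resume lenalidomide at 5 mg reduction in dose". Grade 2 arrhythmia and Grade 2 or 3 hypersensitivity also lead to a hold followed by a 5 mg reduction. Section 10.3.2 separately allows cetuximab delays for skin toxicity and intercurrent illness. Neither Table 6 nor Section 10.3.2 says whether it is suspended in Cycle 1 of the lead-in.

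Under Sections 8.1.1 and 8.1.3, a dose level is accepted when no more than 1 of 6 subjects has a DLT in Cycle 1.

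**The concern.** Section 10.3 makes a DLT the condition for modifying the dose, while the main limb of the DLT definition makes withheld doses the condition for a DLT. Table 6 meanwhile orders holds and reductions for events that cannot be DLTs by grade. A site treating a lead-in subject in Cycle 1 has to decide for itself which text governs.

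That decision feeds the Phase 2a primary endpoint. Six subjects per level, with a cut between 1 and 2 DLTs, fix the lenalidomide dose used in the POC combination arm and the Expansion part. One subject classified differently can change the outcome, and replacement changes who is counted at all.

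**Working it through.** The protocol states no operating characteristic for the lead-in, so there is no figure to reproduce. The check is a comparison of texts, followed by an illustration under assumed rates.

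**Step 1. Events set against the two texts**

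| Event in Cycle 1 | Listed DLT toxicity in 8.1.2? | Table 6 |
|---|---|---|
| Neutropenia, Grade 3, not febrile | No | Hold, then 5 mg lower |
| Thrombocytopenia, Grade 3 | No | Hold, then 5 mg lower |
| Arrhythmia, Grade 2 | No | Hold, then 5 mg lower |
| Hypersensitivity, Grade 2 | No | Hold, then 5 mg lower |
| Neutropenia, Grade 4 | Yes | Hold, then 5 mg lower |
| Thrombocytopenia, Grade 4 | Yes | Hold, then 5 mg lower |

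For the first four rows no DLT exists, so Section 10.3 bars modification while Table 6 orders it.

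**Step 2. Two readings of modification in Section 10.3**

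- *It includes holds*, as Table 6's column heading suggests. No dose may then be withheld before a DLT, so the missed-dose limb cannot arise from a permitted hold. Only the non-resolution route remains.
- *It means reduction only*, as the section title suggests by naming interruption separately. Holds are then allowed and the missed-dose limb works. Table 6 still orders a 5 mg reduction after the non-DLT events in Step 1, which Section 10.3 bars.

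**Step 3. How the same event is classified**

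| Event | Held, 7 or more lenalidomide days missed | Dosed through |
|---|---|---|
| Not a listed DLT toxicity | Replaced | Evaluable, no DLT |
| Listed DLT toxicity | DLT | DLT only if unresolved |

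Table 6 ties hematologic holds to a weekly blood count, so a hold can readily reach 7 days.

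**Step 4. Synopsis against body**

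Both texts require reassessment within 7 days and count non-resolution as a DLT. Only Section 8.1.2 adds "or within 7 days of scheduled start of Cycle 2 Day 1 will be considered a DLT". The difference matters most late in the cycle. A toxicity starting on Day 23 or later can cost at most 28 − 22 = 6 lenalidomide days, below the 7-day threshold, and the last Cycle 1 cetuximab dose is on Day 22. Its classification therefore rests on the non-resolution sentence, which is where the two texts differ.

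**Step 5. Illustration only**

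P(level accepted) = P(X ≤ 1), with X ~ Binomial(6, p), = (1 − p)^6 + 6p(1 − p)^5. Every rate below is assumed.

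- Listed toxicity in 30% of subjects. If all are held and reach the threshold, p = 0.30 and P = 0.118 + 0.303 = 0.42. If none is held and only the unresolved share (30% to 70%) counts, p = 0.09 to 0.21 and P = 0.905 to 0.631.
- Listed toxicity in 20%: 0.655 against 0.954 to 0.800. In 40%: 0.233 against 0.844 to 0.464.
- Replacement, with a DLT rate of 20% among enrolled subjects. If a further 10% to 30% are held for non-DLT events and replaced, the rate among evaluable subjects is 0.20/0.90 = 0.222 to 0.20/0.70 = 0.286, and P = 0.601 to 0.452. If they are dosed through and counted as non-DLT, P = 0.655.

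**The case against.** The best defence combines two points. First, modification can mean a change of dose level. Section 10.3 elsewhere names interruptions and reductions separately. Section 8.1.2 presupposes that Cycle 1 doses can be missed, and it ties a lower lenalidomide dose to subjects who have had a DLT. Second, a specific rule for Cycle 1 of Phase 2a would ordinarily override a general table of guidelines without being repeated in every row. Taken together, holds are allowed and Table 6's reductions are suspended until a DLT, and nothing is circular. This is a coherent reading. But the protocol does not state it, and Table 6's own column heading points the other way.

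Several stronger readings are tempting, and the documents do not support them:

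- *The three texts cannot be followed together and the definition is fully circular.* The circularity depends on counting holds as modifications, and the non-resolution route to a DLT exists on either reading.
- *Subjects must be dosed through toxicity.* Section 10.6 lets the investigator stop product for adverse events that may cause severe or permanent harm or that rule out continuing it.
- *One event can end as no DLT, replaced or DLT.* For hematologic events, grade separates the last two: a long hold for non-febrile Grade 3 cytopenia leads to replacement, and one for Grade 4 to a DLT.
- *Late-cycle toxicities have no common rule.* The synopsis shares the 7-day reassessment and the general non-resolution clause; only the Cycle 2 phrase is missing.
- *The probabilities measure the damage.* Any rule that accepts at most 1 of 6 is sensitive to the DLT rate, and nothing in the protocol shows how far site practice would move that rate.

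**Conclusion.** The inconsistency stands on the text alone and needs no assumption. Section 10.3 and Table 6 give different instructions in lead-in Cycle 1 for at least four event types that are not listed DLT toxicities, and neither common reading of modification reconciles Section 8.1.2, Section 10.3 and Table 6 as written. The synopsis and Section 8.1.2 also carry different DLT definitions. This is an ambiguity with more than one defensible reading; it does not make the lead-in impossible to run.

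Its importance comes from the decision rule: with 0-1 versus 2 or more DLTs in 6, one subject classified or replaced differently can change the dose carried forward. The size of the effect is unknown. The figures above show only that, under assumed rates, the handling of holds could move the chance of accepting a level materially.

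**What to change.** Reconcile the synopsis DLT definition, Section 8.1.2, Section 10.3, Table 6 and Section 10.3.2 before the first lead-in subject is treated:

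1. State in Section 10.3 whether dose modification includes holds.
2. State there whether the holds and reductions in Table 6 and Section 10.3.2 apply in Cycle 1 of Phase 2a, and make the Table 6 column heading agree.
3. Use one identical DLT definition in synopsis and body, settling whether the Cycle 2 clause belongs in it.

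The sponsor's clinical team decides which rule stands; none is proposed here. The cost is protocol wording, with no added visits or subjects.

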### 10.3.1. Lenalidomide Dose Modification or Interruption

**Table 6: Dose Modification Guidelines for Lenalidomide**

| Toxicity                                                            | Grade | Dose Modification                                                                                                                                                                                                                                                                                    |
|---------------------------------------------------------------------|-------|------------------------------------------------------------------------------------------------------------------------------------------------------------------------------------------------------------------------------------------------------------------------------------------------------|
| Rash                                                                | 3     | Hold lenalidomide until resolution to $\leq$ Grade 2; at first occurrence resume at same dose of lenalidomide; at second occurrence resume lenalidomide at 5 mg reduction in dose. Further dose reductions are permitted to a minimum of 5 mg.
If rash is desquamating, discontinue lenalidomide. |
|                                                                     | 4     | Discontinue lenalidomide.                                                                                                                                                                                                                                                                            |
| Sinus bradycardia, atrial fibrillation or other cardiac arrhythmias | 2     | Hold lenalidomide until resolution to $\leq$ Grade 1, resume lenalidomide at 5 mg reduction in dose. Additional dose reductions are permitted to a minimum of 5 mg.                                                                                                                                  |
|                                                                     | 3 / 4 | Discontinue lenalidomide.                                                                                                                                                                                                                                                                            |
| Neutropenia                                                         | 3 / 4 | Hold lenalidomide, CBC weekly until resolution to $\leq$ Grade 2, resume lenalidomide at 5 mg reduction in dose. Additional dose reductions are permitted to a minimum of 5 mg.                                                                                                                      |
| Thrombocytopenia                                                    | 3 / 4 | Hold lenalidomide, CBC weekly until resolution to $\leq$ Grade 2, resume lenalidomide at 5 mg reduction in dose. Additional dose reductions are permitted to a minimum of 5 mg.                                                                                                                      |
| Venous thrombosis or embolism                                       | 3     | Continue lenalidomide and anticoagulate.                                                                                                                                                                                                                                                             |
|                                                                     | 4     | Discontinue lenalidomide and anticoagulate.                                                                                                                                                                                                                                                          |
| Allergic reaction or hypersensitivity                               | 2 / 3 | Hold lenalidomide until resolution to $\leq$ Grade 1; resume lenalidomide at 5 mg reduction in dose. Additional dose reductions are permitted to a minimum of 5 mg.                                                                                                                                  |
|                                                                     | 4     | Discontinue lenalidomide.                                                                                                                                                                                                                                                                            |
| Other non-hematological toxicity assessed as lenalidomide-related   | 3 / 4 | Hold until resolution to $\leq$ Grade 2; resume lenalidomide at 5 mg reduction in dose. Additional dose reductions are permitted to a minimum of 5 mg.                                                                                                                                               |

### 10.3.2. Cetuximab Dose Modification or Interruption

#### 10.3.2.1. Allergic/hypersensitivity Reactions

The investigator must treat all cases of allergic/hypersensitivity reaction with the best available medical measures. Based on previous experience with cetuximab allergic/hypersensitivity reactions, the treatment guidelines given in [Table 7](#).

**Table 7: Treatment Adjustment for Cetuximab-Related Allergic/Hypersensitivity Reactions**

| CTC Grade Allergic/hypersensitivity reaction                                                                                                                                                | Treatment                                                                                                                                                                                                                                                                                                                                                          |
|---------------------------------------------------------------------------------------------------------------------------------------------------------------------------------------------|--------------------------------------------------------------------------------------------------------------------------------------------------------------------------------------------------------------------------------------------------------------------------------------------------------------------------------------------------------------------|
| Grade 1
Transient rash, drug fever <38°C                                                                                                                                                 | Decrease the cetuximab infusion rate by 50% and monitor closely for any worsening
The total infusion time for cetuximab at the weekly dose should not exceed 240 minutes                                                                                                                                                                                        |
| Grade 2
Urticaria, drug fever ≥38°C and/or asymptomatic bronchospasm                                                                                                                     | Stop cetuximab infusion
Administer bronchodilators, oxygen, etc. as medically indicated
Resume infusion at 50% of previous rate once allergic/hypersensitivity reaction has resolved or decreased to grade 1 in severity, and monitor closely for any worsening                                                                                              |
| Grade 3 or Grade 4
Grade 3: Symptomatic bronchospasm, requiring parenteral medication, with or without urticaria; hypersensitivity-related edema, angioedema

Grade 4: Anaphylaxis | Stop cetuximab infusion immediately and disconnect infusion tubing from the subject
Administer epinephrine, bronchodilators, antihistamines, glucocorticoids, intravenous fluids, vasopressor agents, oxygen, etc., as medically indicated

Subjects have to be withdrawn immediately from treatment and must not receive any further cetuximab treatment |

